### Blinding

Owing to the nature of the sitting Baduanjin intervention, it will be impossible to blind the study investigators and participants. Consequently, blinding will only be implemented for the outcome assessors in this RCT to prevent potential detection bias during data collection. The outcome assessors will not be involved in the participant recruitment process. To ensure objective and unbiased results, the people in charge of data collection and analysis will not be informed of the group details.

### Experimental Group

The participants in the experimental group will receive the sitting Baduanjin program. The sitting Baduanjin intervention was developed according to the characteristics of CRF under the guidance of the *zangfu* theory of traditional Chinese medicine and the *qi*-blood meridian theory. In addition, we improved the original standing Baduanjin workout by integrating relevant movements. This plan was revised through 2 rounds of expert consultation, resulting in the improved sitting Baduanjin intervention.

The sitting Baduanjin workout consists of 8 movements, which involve the upper limbs, head and neck, and spine, as well as organized breathing. A preparation and closing posture are added before and after the 8 movements to prepare the patient and ensure their safety [23]. The movements of the sitting Baduanjin workout were tested among patients with advanced cancer for preliminary feasibility and safety. The detailed movements of sitting Baduanjin are shown in Table 1.

**Table 1. T1:** The movements of sitting Baduanjin.

Movement	Main points of the movement
Preparation posture	The patient sits on a chair with their legs naturally open or on the bed. With the body straight and facing the front, the patient feels calm, at ease, and levitated at the Baihui acupoint. The tongue is pressed against the upper jaw. The patient puts their palms in front of the abdomen, closes their eyes, and breathes slightly and peacefully.
First movement: “hands in the sky to support Sanjiao”	When inhaling, the patient lifts their hands from their chest to the top of their head. When exhaling, the patient drops their hands from both sides of their body to their waist and holds them in front of their abdomen.
Second movement: “drawing the bow to shoot the hawk”	The patient reaches their arms out to the sides with their palms down as if they were holding a bow and arrow. They inhale and then exhale as they draw their arms back, bending their elbows and bringing their hands toward their chest. They hold for a moment and then release by straightening their arms and returning to the starting position.
Third movement: “lifting the arms to regulate the spleen and stomach”	The patient raises the left palm and rotates it through the chest, then brings it upward in front of their face, followed by an inward rotation of the arms to lift it to the upper left side of the head. Simultaneously, they rotate the right palm inward and press it down beside the right hip with their fingertips facing forward. The patient then drops their left hand, lifts their right hand simultaneously, and holds their 2 hands in front of their abdomen. They repeat the same movement on the opposite side.
Fourth movement: “looking backward to relieve the fatigues and 7 injuries”	The patient rotates both arms outward with the palms facing outward, turns their head to the left and back, pauses for a moment, and looks diagonally behind to the left. They rotate both arms inward, press them against their hips, move their fingers forward, and look straight ahead. They repeat the same movement on the opposite side.
Fifth movement: “clearing the heart fire by shaking the head and wagging the tail”	The patient lifts both palms in front of the abdomen and chest, extending them above their head with their fingers facing each other. They lower their arms to both sides, placing their palms on top of their thighs. They raise the center of gravity slightly, then shift it to the right, tilt their upper body to the right, bend down, and visually observe the surface of their right foot. They shift the center of gravity to the left while rotating their upper body from right to front and left, visually observing their right heel. They shift the center of gravity to the right, shake their head backward, slightly retract their jaw, and look ahead. The right-side action is the same as the left-side action but in the opposite direction.
Sixth movement: “move 2 hands down to the leg to strengthen the kidney and lumbar area”	The patient raises both arms forward and upward, with their palms facing forward. They press their palms against their chest with the elbows bent, palms facing downward, and fingers facing each other. They rotate both arms outward with their palms facing upward and then insert the palm fingers under the armpits. They rub their palms inward along the spine to the kidney area and then rub them back and forth. They return their hands to the front of the abdomen through the body.
Seventh movement: “tighten fists to gather strength”	The patient holds both fists at the waist, with the thumb inside and the fist facing upward, and looks straight ahead. They inhale and hold their fists, exhale and clench their left fist with a furious gaze, keep their eyes wide open, grip firmly, inhale, and retract. They exhale and clench their right fist with a furious gaze, keep their eyes wide open, grip firmly, inhale, and retract.
Eighth movement: “rotate shoulders to enhance *yang* and *qi”*	The patient lowers both arms naturally, contracts the abdomen, and expands the chest. They inhale to lift their shoulders and rotate them inward and exhale to lower their shoulders. They inhale to lift their shoulders and rotate them outward and exhale to lower their shoulders.
Closing posture	The patient wipes their face, combs their hair, rubs their ears, and taps their left and right elbow creases.

The program lasts for a total of 16 weeks [12]. In the first week, the participants will attend a training session to learn about sitting Baduanjin by watching a training video, which explains the exercise methods and precautions of sitting Baduanjin. A trained research nurse will then guide the participants to complete sitting Baduanjin according to the video and adjust incorrect movements individually, if any. The training session will include no more than 8 patients. From week 2 to week 16, the participants will perform sitting Baduanjin exercises by themselves once daily for approximately 20 to 30 minutes, including 5 minutes of preparation posture, 12 minutes of sitting Baduanjin, and 5 minutes of closing posture.

To enhance participant compliance, we have established a WeChat group for the experimental group to provide remote supervision. Videos of the sitting Baduanjin exercises and relevant theoretical knowledge will be pushed to patients via WeChat. Participants in the experimental group are required to practice daily, take photos as proof, and upload them via a check-in mini program. This process serves to document their practice duration and facilitates self-monitoring. Their caregivers are also involved to encourage participants to persist in their exercises. During home care, the main responsibility of the caregiver is to remind the participants to do the Baduanjin exercises on time and submit proof of having done the exercises via WeChat. We conduct follow-up visits and phone calls with patients twice a week via WeChat video to inquire about factors that may hinder their activities and resolve them promptly. In addition, participants in the experimental group are requested not to discuss their practice with each other to minimize interference.

### Control Group

Patients randomized to the control group are provided with usual care. They will receive regular health education on exercise and a healthy lifestyle, including seated stretching and breathing exercises. After discharge, they will be provided with material on how to exercise. Participants will be asked to avoid any other traditional Chinese sports activities during the study, with reminders provided at every assessment interval. Considering ethical aspects, once the effectiveness of sitting Baduanjin is established, we will provide it for free to the control group if they are interested.

### Outcome Measurements

#### Primary Outcomes

The primary outcome of this RCT is CRF. The severity of CRF in the daily functioning of the participants will be measured by using the Chinese version of the RPFS. The original scale was developed by Piper [24] in 1989, with its revised Chinese version developed by So et al [25] in 2003. The questionnaire includes 22 items that assess the general level of fatigue using a visual analog scale with values from 0 to 10. It also assesses 4 facets of fatigue: severity, emotional, sensory, and cognitive. A score of 0 indicates no fatigue symptoms, mild fatigue is defined as scores between 1 and 3, moderate fatigue is defined as scores between 4 and 6, and severe fatigue is defined as scores between 7 and 10. The RPFS exhibits Cronbach α coefficients between 0.89 and 0.93 for each subscale and 0.91 for the overall scale [26].

#### Secondary Outcomes

The secondary outcomes include patients’ anxiety, depression, and quality of life.

##### Anxiety

Secondary outcomes encompass anxiety as gauged using the mean score on the 7-item Generalized Anxiety Disorder Scale (GAD-7) [27]. The GAD-7 was developed by Spitzer et al [28] in 2006 for measuring the level of anxiety in patients over the previous 2 weeks. The GAD-7 is a gold-standard measuring instrument for generalized anxiety disorder [27]. It is a rapid, user-friendly, compact, and self-executed screening and diagnostic instrument. The GAD-7 is computed by allocating scores of 0, 1, 2, and 3 to the response categories of “not at all,” “several days,” “more than half the days,” and “nearly every day,” respectively. The total score ranges from 0 to 21. Scores of 5, 10, and 15, respectively, denote cutoff points for mild, moderate, and severe anxiety. The Chinese version of the GAD-7 shows solid internal consistency reliability (Cronbach α ranging from 0.715 to 0.931), along with construct validity and convergent validity [29].

##### Depression

Depression will be gauged by means of the Patient Health Questionnaire–9 (PHQ-9) [30]. The PHQ-9 is a self-administered diagnostic tool for the severity of depression [30]. It is determined by attributing scores of 0, 1, 2, and 3 to the response categories of “not at all,” “several days,” “more than half the days,” and “nearly every day,” respectively. The overall score ranges between 0 and 27. Scores of 5, 10, 15, and 20 stand for the cutoff points for mild, moderate, moderately severe, and severe depression, respectively. The Chinese version of the PHQ-9 exhibits internal consistency reliability (with Cronbach α ranging from 0.729 to 0.891), along with construct validity and convergent validity [31].

##### Quality of Life

Quality of life will be evaluated using the Functional Assessment of Cancer Therapy–General (FACT-G) total score. The scale encompasses 27 items across 4 dimensions: physiological status, social or family status, and functional status, each containing 7 items, and emotional status, containing 6 items. Each item is scored from 0 to 4, with higher scores denoting better quality of life [32]. The FACT-G is accessible in a simplified Chinese version, and adequate psychometric properties have been reported among patients with advanced cancer. The Chinese version of the FACT-G exhibits excellent internal consistency reliability (with Cronbach α from 0.89 to 0.98), along with construct validity and convergent validity [33].

##### Other Measurements

In addition, patient demographics (including gender, age, educational background, marital status, employment status, and household income) and clinical characteristics (such as diagnosis, stage, course of disease, and current treatment) will be collected at baseline.

### Data Collection

The baseline assessments will be conducted by the research nurse who is in charge of participant recruitment and random assignment to groups. All participants will be requested to complete the RPFS, GAD-7, PHQ-9, FACT-G, and demographic data sheet on-site at baseline (T0). The reassessment of the outcomes will be conducted at 12 (T1) and 16 (T2) weeks after baseline. Follow-up data will be gathered via telephone by a research assistant who will be blinded to the participants’ group allocation. The schedule of study outcome assessments is outlined in Table 2.

**Table 2. T2:** SPIRIT (Standard Protocol Items: Recommendations for Interventional Trials) diagram of enrollment, treatment, and assessments over the intervention period.

	Study period					
	Enrollment	Baseline assessment	Allocation	Intervention week 12 (T1)	Intervention week 16 (T2)	
Recruitment						
Eligibility screen	✓					
Informed consent	✓					
Randomization						
Allocation			✓			
Interventions						
Experimental group						
Control group						
Patient-reported outcomes						
Demographic characteristics		✓				
RPFS^a^		✓		✓	✓	
GAD-7^b^		✓		✓	✓	
PHQ-9^c^		✓		✓	✓	
FACT-G^d^		✓		✓	✓	
Adverse effects or events				✓	✓	
Adherence to exercise						

a RPFS: Revised Piper Fatigue Scale.

b GAD-7: 7-item Generalized Anxiety Disorder Scale.

c PHQ-9: Patient Health Questionnaire–9.

d FACT-G: Functional Assessment of Cancer Therapy–General.

### Data Analysis

Statistical analyses will be carried out using SPSS Statistics for Windows (version 23.0; IBM Corp). Demographic data will be summed and presented using appropriate descriptive statistics, such as frequency distributions and means and SDs. The homogeneity of baseline characteristics between the 2 groups will be evaluated using the independent 2-tailed *t* test, chi-square test, or Wilcoxon rank sum test as appropriate. A generalized estimating equation (GEE) model will be implemented for repeated multivariate analysis between the 2 study groups regarding the total scores and domain scores on the RPFS, GAD-7, PHQ-9, and FACT-G. The analysis will be conducted in accordance with the intention-to-treat principle. In case of missing data at random, the missingness will be left unaddressed because the GEE model could yield valid results through analyzing the observed data [34]. Otherwise, multiple imputation will be used for the missing data. Sensitivity analyses will be conducted by comparing results across standard GEE and multiple imputation–based GEE. The significance level for identifying statistical differences will be set at *P*<.05.

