## Results

The study was approved by the Medical Ethics Review Committee of Hunan Cancer Hospital in March 2024 (ethics approval number 2024.50). Before this full-scale RCT, we conducted a pilot study. A total of 24 participants were recruited between March 2025 and April 2025. After the intervention, 18 participants, comprising 9 from the intervention group and 9 from the control group, completed the follow-up evaluation. The retention rate was 75%. The pilot study demonstrated the feasibility and acceptability of sitting Baduanjin for patients with advanced cancer, with potential benefits for relieving fatigue.

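### The missing-data rule places each method one step too far: unweighted GEE is called valid under missing at random, and multiple imputation is kept for when that assumption fails

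*Protocol article*

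**What the plan says.** All of the rule stands in the Data Analysis section of the protocol article.

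- Model: "A generalized estimating equation (GEE) model will be implemented for repeated multivariate analysis between the 2 study groups", applied to total and domain scores. The article names no weighting and no working correlation.
- Under MAR: "the missingness will be left unaddressed because the GEE model could yield valid results through analyzing the observed data".
- In every other case: "Otherwise, multiple imputation will be used for the missing data".
- Sensitivity analysis: "Sensitivity analyses will be conducted by comparing results across standard GEE and multiple imputation–based GEE".
- Analysis set: "The analysis will be conducted in accordance with the intention-to-treat principle".

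Two other places bear on how much this matters. The Sample Size Calculation section allows for 20% dropout. The Results section reports that 18 of 24 pilot participants completed follow-up: "The retention rate was 75" (per cent).

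**The concern.** The article gives a rule and a reason for it, and the reason is wrong in general. There are four problems.

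1. Unweighted GEE on the observed records is valid under MCAR, or when missingness depends only on covariates in the model. If dropout depends on an earlier observed fatigue score, which is the typical MAR case, GEE is protected only when the working correlation is close to the truth.
2. Standard multiple imputation assumes MAR. Keeping it for the case where MAR fails assigns it to the situation that its own assumption excludes.
3. The observed data cannot separate MAR from missing not at random (MNAR). The switch therefore turns on something that cannot be established, and the choice of primary analysis is left until the data have been seen.
4. The sensitivity comparison sets a method that needs MCAR or a good working correlation against a method that needs MAR. Neither shows how the conclusion would move if MAR failed.

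What is at stake is the Revised Piper Fatigue Scale (RPFS) comparison, the primary outcome, in a population where a fifth to a quarter of follow-up may be missing.

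**Working it through.** **Inputs from the article.** 1:1 allocation; 49 per group; visits at baseline (T0), week 12 (T1) and week 16 (T2); effect size 0.69; power 0.85; two-sided 0.05; planned dropout 20%; pilot 18 of 24 retained.

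**The plan's own figures.** The missing-data rule has no figure of its own. The figures around it reproduce: a two-sample t test with d = 0.69 needs 39 per group (power 0.853 by the noncentral t); 39 / (1 − 0.20) = 48.75, so 49 per group and 98 in total; 18 / 24 = 75% retained, so 25% lost.

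**Where each method belongs.**

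| Missingness | The article uses | Generally valid |
|---|---|---|
| MCAR, or depends only on modelled covariates | not separated from MAR | observed-data GEE |
| MAR | observed-data GEE | imputation, weighted GEE, or a likelihood-based mixed model |
| MNAR | multiple imputation | no standard method; a sensitivity analysis such as delta adjustment |

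**Assumptions for the size (not in the article).** Outcome SD 1; correlation between visits 0.5 or 0.7, exchangeable or AR(1); true difference −0.5 SD at T1 and −0.69 SD at T2; about 25% missing at T2 in each arm; where dropout depends on T1 fatigue, log odds of 1 per SD.

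**Formula for independence GEE.** With a saturated arm-by-visit model, the T2 estimate is the difference in completers' means. With ρ the T1–T2 correlation,

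bias = ρ × (T1 shift among completers, exercise arm − T1 shift among completers, control arm).

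Under the assumed slope, completers in an affected arm have a mean T1 score about 0.215 SD below that of the whole arm.

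- Exercise arm only: 0.5 × (−0.215) = −0.11; 0.7 × (−0.215) = −0.15.
- Control arm only: the sign changes, giving +0.11 and +0.15.
- Same dependence in both arms: the shifts cancel, giving 0.
- Opposite dependence: ρ × (−0.43) = −0.22 and −0.30.

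**Large-sample simulation (1,000,000 records, true T2 difference −0.69).**

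| Dropout depends on T1 fatigue | Independence GEE | Exchangeable GEE | True-correlation GEE | Imputation under MAR |
|---|---|---|---|---|
| same way in both arms | −0.69 | −0.69 | −0.69 | −0.69 |
| exercise arm only | −0.80 to −0.84 | −0.69 to −0.70 | −0.69 to −0.70 | −0.69 to −0.70 |
| opposite ways | −0.90 to −0.99 | −0.69 to −0.715 | −0.69 | −0.69 |

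The exercise-only bias of 0.11 to 0.15 SD is about 15 to 22% of 0.69. An exchangeable structure is unbiased when true. When the truth is AR(1), it is off by about 0.01 SD in the exercise-only case and up to 0.025 SD in the opposite-ways case.

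**In RPFS points.** With an assumed SD of 1.8, dropout in the exercise arm tied to the last observed score and varied assumptions, separate simulations of independence GEE gave 0.18 to 0.31 points: 0.18 / 1.8 = 0.10 SD and 0.31 / 1.8 = 0.17 SD. Exchangeable or correct structures gave about 0.02 points: 0.02 / 1.8 = 0.01 SD.

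**Effect on type I error.** In the same kind of setting with no true effect, independence GEE at 49 + 49 rejected in about 7 to 11% of trials; exchangeable and correct structures gave 5 to 6%. A hand check agrees. With 49 × 0.75 = 36.75, about 37 completers per arm, SE = √(2/37) = 0.2325 SD. A bias of 0.11 SD is 0.47 SE and gives two-sided rejection of about 7.6%; 0.15 SD is 0.65 SE and gives about 9.9%.

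**The case against.** The strongest case is that this is only loose terminology. Applied writers often say that data are missing at random when they mean completely at random. On that reading, GEE on observed data followed by imputation otherwise is a conventional order, and MCAR can at least be partly checked. This softens the point but does not remove it. The article does not say MCAR, a check can reject MCAR but cannot confirm it, and imputation would still be the answer to everything else, including MNAR.

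Second, the larger bias figures need an independence working correlation. The article names no structure, and that detail is commonly left to a fuller document, so its absence is no fault here. This stands: the size is conditional. But the article claims validity without that condition.

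Third, a reader might infer that the error favours Baduanjin, because tired patients give up daily exercise. The documents do not support this. Stopping exercise is not the same as missing an outcome: follow-up is by telephone, and the analysis is by intention to treat. Regular contact in the exercise arm may even help retention there. The pilot had 9 completers in each group. That does not prove equal dropout mechanisms, but it gives no evidence of unequal ones. Fatigue-related loss in controls alone would bias the other way.

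Fourth, the planned comparison of GEE with imputation-based GEE could partly expose an MAR bias, provided the imputation uses earlier scores. This also stands. The article does not say which result prevails if they differ, and the comparison does not address MNAR.

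**Conclusion.** The point holds as an error in the stated rule and its stated reason; it should be fixed. A reader might call the rule reversed. That is too strong: each method is placed one step beyond where it is valid, and the order is not turned round. A reader might also conclude that the primary result will be biased toward efficacy. The documents support only that it can be biased, with the direction unknown.

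If dropout depends on earlier fatigue in one arm only, the bias in the RPFS contrast is about 0.1 to 0.17 SD with an independence working correlation, in a direction set by the affected arm, and about 0.01 SD or less with an exchangeable or correct structure. Opposite dependence in the two arms would be worse (0.21 to 0.30 SD with independence); equal dependence gives a bias near zero. The SD, correlations and dropout slopes behind these figures are assumptions; only the dropout rates of 20% and 25% come from the article. No MNAR bias has been quantified. That the rule is wrong as written does not depend on the simulations.

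**What to change.** 1. Delete the switch between the at-random case and the rest.
2. Fix one primary analysis of the RPFS total in advance that is valid under MAR. Either of these would do: GEE on multiply imputed data, with arm and the T0 and T1 scores in the imputation model; or a likelihood-based mixed model for repeated measures.
3. Limit the validity claim for observed-data GEE to MCAR (or missingness explained by modelled covariates), keep that analysis as a secondary comparison, and state that the primary result stands if the two differ.
4. Add a delta-adjusted imputation as the MNAR sensitivity analysis: shift the imputed RPFS scores by increasing amounts, by arm, and report where the conclusion changes.

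The cost is revised wording and a little more analysis work. No new data are needed. The change should be made before outcome data are examined, so that the primary analysis is not chosen in the light of the results.
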